##### Primary endpoints

GV. Defined as the standard deviation of the mean blood glucose level for each patient [17]. For the main analysis, we will use the GV value recorded within the first 48 h after stroke onset. We will conduct an exploratory analysis to evaluate the GV between 48 and 96 h.Mortality: in-hospital and at 3 months.

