##### Sample size estimates

Based on the data from the GLIAS-II study, [11] conducted in a similar setting and using nQuery Advisor software (Statistical Solutions Ltd., Cork, Ireland), we calculated that a sample of 340 patients will be required to achieve 80% statistical power and a confidence level alpha of 0.05 to detect a significant effect of GV on mortality at 3 months.

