### Statistical analysis

The statistical analysis will be performed with advice from the Department of Biostatistics of La Paz University Hospital. ﻿For the continuous variables, the following information will be provided: number of participants, mean, standard deviation, median, minimums, maximums and 25% and 75% quartiles. For the categorical variables, the frequency distribution and 95% confidence interval (CI), if applicable, will be provided. The analysis of the prognostic influence of GV on stroke outcomes will be performed in an exploratory manner without assumptions. We will first analyze GV as a continuous variable, comparing it with primary and secondary endpoints using Student’s t-test or the Mann–Whitney U test, as appropriate. We will also compare GV according to the various insulin types and administration routes applied to the patients according to the physician’s discretion. The comparisons will be performed with the one-way analysis of variance test. Secondly, we will perform a step forward logistic regression analysis for the endpoints that achieved a difference with a *P* value < 0.1 in the mean comparison tests, adjusting for age and baseline National Institutes of Health Stroke Scale score. The results will be expressed as odds ratios (OR) with 95% CI. In case of lack of homogeneity in the variances, we will use non-parametric tests (Kruskal–Wallis and Mann–Whitney test).

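### Unequal variances are made the reason to switch to Mann-Whitney and Kruskal-Wallis, but with unequal group sizes these tests do not hold their level as tests of location

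*Protocol article*

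**What the plan says.** All of this stands in the protocol article under Statistical analysis, unless noted.

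- GV is analysed first as a continuous variable, "comparing it with primary and secondary endpoints using Student’s t-test or the Mann–Whitney U test, as appropriate".
- GV is also compared across the insulin types and routes that patients happen to receive: "The comparisons will be performed with the one-way analysis of variance test".
- Endpoints go on to logistic regression if they reach a P "value < 0.1 in the mean comparison tests, adjusting for age and baseline National Institutes of Health Stroke Scale score".
- The section closes with the fallback rule: "In case of lack of homogeneity in the variances, we will use non-parametric tests", and it names Kruskal-Wallis and Mann-Whitney as those tests.

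No test that allows unequal variances is named. The section calls the prognostic analysis exploratory. Under Primary endpoints, the outcome that splits the patients is "Mortality: in-hospital and at 3 months". Under Sample size estimates, "a sample of 340 patients will be required to achieve 80% statistical power". The article gives no expected mortality, no SD of GV by outcome and no insulin group sizes.

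**The concern.** Rank tests are a remedy for non-normal data. Their null variance is derived for identical distributions, so a difference in spread breaks it just as it breaks the pooled variance of Student's t. The rule therefore sends the analyst to these tests in the one situation where, as tests of location, they lose their level. The plan does use them as tests of location, because it refers to the screening step as a comparison of means.

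Two things depend on these P values: which endpoints pass the 0.1 screen, and the comparison of GV by insulin type and route, where physicians' choices set the group sizes. A wrong level can let endpoints through too easily or hold them back, depending on which group varies more.

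**Working it through.** **Inputs from the article.** N = 340; alpha 0.05 (two-sided assumed); screening threshold 0.1; tests as listed above. The figure of 340 cannot be recomputed, because its effect size, SD and mortality are not given. The article states no error rate for the fallback tests that could be reproduced.

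**Assumed inputs.** Deaths m = 17, 34 or 51 (5%, 10%, 15%), survivors n = 340 − m. SD ratio s, deaths to survivors, = 0.5, 1, 1.5 or 2. Normal data with equal means, hence equal medians.

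**Step 1: closed form for Mann-Whitney.** On the scale of the estimated probability that one group exceeds the other, the test assumes the variance

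V0 = (m + n + 1) / (12mn).

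The actual variance is approximately

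V = v1/m + v2/n, with v1 = arcsin(s²/(1+s²))/(2π) and v2 = arcsin(1/(1+s²))/(2π).

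At s = 1 both v1 and v2 equal 1/12 and the test is correct. The real level is 2[1 − Φ(1.96/√(V/V0))].

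- *17 deaths, s = 2.* v1 = arcsin(0.8)/(2π) = 0.1476; v2 = arcsin(0.2)/(2π) = 0.0321. V = 0.1476/17 + 0.0321/323 = 0.00878. V0 = 341/(12 × 17 × 323) = 0.00518. V/V0 = 1.70, square root 1.303. Level = 2[1 − Φ(1.505)] = 13.2%.
- *17 deaths, s = 0.5.* V = 0.0321/17 + 0.1476/323 = 0.00234. V/V0 = 0.453, square root 0.673. Level = 2[1 − Φ(2.91)] = 0.4%.

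The smaller group dominates V, so its spread sets the direction.

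**Step 2: simulation, 10,000 runs per cell.** Rejection rates in %:

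| Deaths : survivors | SD ratio | Mann-Whitney at 5% | Mann-Whitney at 10% | Student's t at 5% | Welch at 5% | Welch at 10% |
|---|---|---|---|---|---|---|
| 17 : 323 | 0.5 | 0.3 | 1.1 | 0.0 | 4.5 | 9.4 |
| 17 : 323 | 1 | 4.8 | 9.5 | 4.6 | 4.9 | 9.5 |
| 17 : 323 | 1.5 | 10.2 | 16.7 | 17.3 | 5.1 | 9.9 |
| 17 : 323 | 2 | 13.3 | 20.3 | 28.4 | 5.0 | 10.0 |
| 34 : 306 | 0.5 | 0.4 | 2.1 | 0.1 | 4.8 | 9.8 |
| 34 : 306 | 1 | 5.2 | 10.0 | 5.2 | 5.4 | 10.4 |
| 34 : 306 | 1.5 | 9.2 | 16.0 | 14.8 | 4.8 | 9.8 |
| 34 : 306 | 2 | 12.7 | 19.8 | 24.1 | 5.1 | 9.8 |
| 51 : 289 | 0.5 | 1.1 | 3.3 | 0.3 | 4.9 | 9.6 |
| 51 : 289 | 1 | 4.9 | 10.2 | 4.9 | 5.0 | 10.0 |
| 51 : 289 | 1.5 | 8.8 | 15.0 | 13.5 | 5.0 | 9.7 |
| 51 : 289 | 2 | 11.9 | 19.4 | 21.3 | 5.1 | 10.3 |
| 170 : 170 | 2 | 5.9 | 11.1 | 4.9 | 4.9 | 9.8 |

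Other runs moved the extremes slightly. That gives the rounded ranges 9% to 14% (at 5%) and 15% to 22% (at 0.1) for SD ratios 1.5 to 2, 0.2% to 1.3% for ratio 0.5, and about 14% to 30% for Student's t at ratios 1.5 to 2. Brunner-Munzel gave 4.6% to 5.5% on such data.

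**Step 3: the rule as a two-stage procedure.** The article does not say how lack of homogeneity is judged. If it is Levene's test at 0.05, then Mann-Whitney or t, the level at SD ratio 2 is 12.8%, 11.6% and 12.8% for 17, 34 and 51 deaths (2,000 runs).

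**Step 4: Kruskal-Wallis, assumed groups of 200/100/40.** SDs 1/1.5/2 give 10.2%. SDs 2/1.5/1 give 2.5%. Equal SDs give 4.6%. Near-equal groups with SDs 1/2/3 give 5.8%, and three groups of 10 with the same SDs give 5.7%, so the balanced animal groups are not the problem. Welch's ANOVA gives 4.6% to 5.4% throughout.

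**Step 5: skewed data.** With lognormal data, equal medians and log-SDs 0.7 (deaths) and 0.4, Mann-Whitney rejects in 12.1%, 11.2% and 10.2% for 17, 34 and 51 deaths. On the log scale this is the normal case with SD ratio 1.75, and ranks do not change under the log. Welch on raw GV with equal means and the same log-SDs gives 9.2%, 7.8% and 7.3%. Welch therefore belongs on the log scale if GV is skewed.

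**The case against.** Several counter-arguments carry weight.

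- **Direction.** A reader might infer that the plan's tests are anti-conservative as written. The article does not support that. It gives neither mortality nor spread by outcome, and the sign reverses if the smaller group varies less. Nor does it describe a small intravenous-insulin group set against a large untreated one; it mentions only the types and routes applied.
- **The null hypothesis.** If GV is unrelated to death, its whole distribution is the same in both groups and Mann-Whitney holds its level. Equal means with unequal spread already imply some relation between GV and death. The excess rejections are errors about location, not false claims of any association at all.
- **The alternative in the plan.** On the same data Student's t is worse: 28.4% against 13.3% at 17 deaths and SD ratio 2. The switch reduces the distortion.
- **Skew.** GV is a per-patient SD, so it is positive and probably skewed (an assumption). If groups differ by a multiplicative shift, raw variances differ and a rank test is valid. With 34 : 306, log-SD 0.5 and a log shift of 0.25, power is 0.78 for Mann-Whitney, 0.67 for Welch on raw GV and 0.79 for Welch on log(GV).
- **Consequence.** The section is labelled exploratory, and what it reports is an adjusted odds ratio. In an unadjusted simulation at SD ratio 2, replacing the screen lowers the rate of passing both screen and logistic P < 0.05 only from 0.15–0.18 to about 0.10. The logistic model alone rejects in 0.22–0.29.
- **Preliminary test.** A formal variance test is an inference; how homogeneity is judged may be set elsewhere.

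These points limit the size and direction of the concern. They do not make unequal variance a sound reason for choosing a rank test, and the skew argument favours a log scale fixed in advance.

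**Conclusion.** The stated rule is the wrong remedy, in a limited and conditional sense. As location tests with unequal group sizes and unequal spread, Mann-Whitney and Kruskal-Wallis miss their level. Mann-Whitney runs at roughly two to three times nominal 5% if the deaths vary 1.5 to 2 times as much as survivors, and far below nominal if they vary half as much. This rests on assumed deaths of 5% to 15%, assumed SD ratios and equal centres; with balanced groups the distortion is mild (5.9% at SD ratio 2). It bears on the 0.1 screen and the insulin comparison, not on the adjusted logistic model, and it does not invalidate the study. It is a fault in a rule the article states, not a detail left to an analysis plan. The change is worth making because it is cheap and works under either direction.

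**What to change.** Replace the last sentence of Statistical analysis with: *GV will be compared by Welch's t-test (two groups) and Welch's ANOVA (more than two groups), on log(GV), a scale fixed in advance, whether or not variances appear equal; if a rank test is wanted for two groups, Brunner-Munzel will be used.* The two earlier places in that section that name Student's t, Mann-Whitney and one-way ANOVA then need to be aligned with it.

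The cost is a very small loss of power when variances are in fact equal, and differences are read as ratios of geometric means. No extra data or patients are needed. The change corrects the screen and the insulin comparison only.

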## DIscussion

To our knowledge, few studies have used continuous glucose monitors in acute IS [7, 8, 26–28]. A relationship has been found between GV (by means of the standard deviation of mean glucose levels) and infarct growth [8], as well as between GV and early neurological deterioration [29]. The main limitations of the prior studies using CGM in acute stroke are their monocentric settings, the lack of analysis of the effect of insulin administration on GV and the heterogeneity in the index used to express GV, given there is no widely accepted optimal index [30]. The GLIAS-III study is designed to overcome those limitations, with a prospective and multicenter approach, and is aimed at recruiting more than 300 patients. Moreover, the development of a parallel preclinical study using an animal model of permanent MCAO will increase our knowledge of the effect of insulin administration on GV, functional outcomes, lesion size, brain damage and repair-related markers.

## Data Availability

After the completion of the trial, raw data will be deposited in an institutional repository and final results will be published in Open Access journals.
